### 10.1 Test-negative design (TND)

#### Inclusion criteria

- Aged  $\geq 18$  years (aged  $\geq 12$  years once Moderna COVID-19 vaccine is authorized in this age group) as of date of specimen collection for the SARS-CoV-2 test (Day 0)
- KPSC member for  $\geq 12$  months prior to Day 0 (Day -365 to Day 0, inclusive, and allowing a 31-day gap)
- Tested positive for SARS-CoV-2 by PCR at KPSC with specimen collected on or after 3/1/2021 and sent for WGS, without a history of a COVID-19 diagnosis code or SARS-CoV-2 positive molecular test in the 90 days prior to the test; or tested negative for SARS-CoV-2 by PCR with specimen collected on or after 3/1/2021

### Exclusion criteria

- Receipt of a COVID-19 vaccine other than Moderna COVID-19 vaccine on or prior to the date of specimen collection for the SARS-CoV-2 test
- Receipt of 2 doses of Moderna COVID-19 vaccine <24 days apart
- Receipt of a Moderna COVID-19 vaccine <14 days prior to the date of specimen collection for the SARS-CoV-2 test (Day -13 to Day 0, inclusive)
- Receipt more than 2 doses of Moderna COVID-19 vaccine on or prior to the date of specimen collection for the SARS-CoV-2 test
- Having a history of a COVID-19 diagnosis code or SARS-CoV-2 positive molecular test between 12/18/2020 and 2/28/2021, inclusive.

### Matching

**Test-positive cases:** Individuals who meet the inclusion/exclusion criteria, and have a positive SARS-CoV-2 test on or after 3/1/2021 with the specimen sent for WGS will be defined as cases. For individuals who have more than one positive test after 3/1/2021, sequencing data from the first specimen will be included in analyses. The date of specimen collection for the positive test will be referred to as the index date.

**Test-negative controls:** Individuals who meet the inclusion/exclusion criteria, have a negative SARS-CoV-2 molecular test on or after 3/1/2021, and do not have a positive test on or after 3/1/2021 will be defined as controls. Controls will be randomly selected and matched, in separate processes, for the 2-dose VE analysis and the 1-dose VE analysis.

Individual matching will be applied for both the 2-dose analysis and 1-dose analysis. Controls will be matched to cases by age group (12-17 years [once Moderna COVID-19 vaccine is authorized in this age group], 18-44 years, 45-64 years, 65-74 years, and 75+ years at specimen collection date), sex, race/ethnicity (Non-Hispanic White, Non-Hispanic Black, Hispanic, Non-Hispanic Asian, and Other/Unknown), and specimen collection date (+/- 10 days). The matched date of specimen collection for the negative test will be the index date for the matched control.

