| Number of patients tested for SARS-CoV-2 with RT-PCR test                       | 48,290      | 825,670 | 184,197 | 1,058,157 |
| Number of patients with a positive SARS-CoV-2 RT-PCR test                       | 13,788      | 200,403 | 24,452  | 238,643   |
| Number of patients with a COVID-19 diagnosis                        | 15,807      | 247,628 | 31,960  | 295,395   |
| Number of patients admitted to hospital with a COVID-19 diagnosis   | 87          | 10,871  | 7,980   | 18,938    |
| Number of patients admitted to ICU with a COVID-19 diagnosis        | 13          | 2,928   | 2,227   | 5,168     |
| Number of deaths within 31 days after the first COVID-19 diagnosis  | 1           | 715     | 2,038   | 2,754     |

A COVID-19 diagnosis includes those with a positive SARS-CoV-2 RT-PCR test result or a COVID-19 diagnosis code only.

As of December 31, 2020, over 1 million SARS-CoV-2 RT-PCR tests had been performed at KPSC, of which 17.4% were among individuals aged ≥65 years and 4.6% were among adolescents aged 12-17 years (Table 2). There were 238,643 members testing positive (13,788 members aged 12-17 years and 24,452 members aged ≥65 years). Additional members were diagnosed with COVID-19 based on positive test results outside of KPSC or clinical presentation and contact history, for a total of 56,752 members with a COVID-19 clinical diagnosis only. Approximately 25.0% (7,980/31,960) of COVID-19 patients aged ≥65 years were hospitalized, compared to only 4.4% (10,871/247,628) who were hospitalized among patients aged 18-64 years and 0.6% (87/15,807) who were hospitalized among patients aged 12-17 years. The proportion of COVID-19 patients being admitted to the ICU was 7.0% in patients aged ≥65 years versus 1.2% in patients aged 18-64 years. The proportion of COVID-19 patients who died within 31 days after a COVID-19 diagnosis or a positive test was 6.4% in patients aged ≥65 years versus 0.29% in patients aged 18-64 years.

As of July 2021, asymptomatic individuals who receive a COVID-19 test at KPSC may include individuals without COVID-19 symptoms who require or request testing. Both vaccinated and unvaccinated individuals are required to be tested for SARS-CoV-2 prior to KPSC procedures or admission. In addition, asymptomatic individuals can request testing (regardless of vaccination status) for any of the following reasons: travel, exposure to or close contact with a COVID-19-

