### 7.2 Outcome Definitions

The primary outcomes for this study are:

1. COVID-19 diagnosis will be defined as a SARS-CoV-2 positive molecular test or a COVID-19 diagnosis code (Primary Objective 1, Secondary Objectives 1-12, 14)
2. Severe COVID-19 disease includes COVID-19 hospitalization (hospitalization with a SARS-CoV-2 positive test or a COVID-19 diagnosis, or a hospitalization occurring  $\leq 7$  days after a SARS-CoV-2 positive test, with chart review to confirm severe COVID-19 symptoms) and COVID-19 mortality (death during COVID-19 hospitalization) (Primary Objective 2, Secondary Objectives 13, 15)

We will ascertain the first occurrence of COVID-19 diagnosis or severe COVID-19 disease  $\geq 14$  days after the index date.

Incident COVID-19 cases (identified through diagnosis code or positive molecular test) will be separated into symptomatic and asymptomatic COVID-19 cases. COVID-19 symptoms will be identified using a natural language processing (NLP) algorithm (currently being submitted for publication). The NLP algorithm will be applied to clinical notes before and after the incident COVID-19 diagnosis date to search for COVID-19 related symptoms. COVID-19 cases with no symptoms identified will be considered asymptomatic cases.

Positive SARS-CoV-2 tests conducted for surveillance of asymptomatic individuals will also be used as a preliminary approach to identify asymptomatic COVID-19 cases until the NLP algorithm is finalized. The use of testing data in asymptomatic individuals will facilitate assessment of VE against asymptomatic COVID-19 for the first interim analysis, whereas the

more comprehensive NLP approach will require more time to apply and will be used for subsequent analyses.

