## 13 Limitations

This study has several potential limitations. Misclassification of the exposure is possible if COVID-19 vaccines were received outside of the KPSC system. However, external COVID-19 vaccination can be captured in the KPSC EHR data by manual entry and electronic updates from the California Immunization Registry (CAIR) (for which KPSC has a proactive mechanism in place for obtaining regular updates from CAIR). Misclassification of COVID-19 outcomes is also possible due to imperfect capture and sensitivity of SARS-CoV-2 molecular diagnostic tests. For variant VE analyses (Secondary Objectives 16-17), sequencing may be unsuccessful if viral loads are low, which may be more common among vaccinated vs. unvaccinated individuals. However, samples with unsuccessful sequencing may also be considered a test-positive case group for analysis. For patients with COVID-19 symptoms, sensitivity of molecular diagnostic tests is generally high (>90%). Efforts are made to ask patients about positive tests conducted outside of KPSC and to document in the EHR with internal diagnosis codes. In addition, we will be unable to capture some potential confounders, such as occupational risk exposures, behavioral factors (e.g., masking, distancing, handwashing), and residential factors (e.g., congregate settings) that impact an individual's risk for COVID-19. Thus, despite all efforts to ensure comparability, there may be some unmeasured differences between vaccinated and unvaccinated cohorts. Some secondary analyses may be underpowered; their meaningfulness will depend on uptake of Moderna COVID-19 vaccine in these patient populations.

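### The 90-day COVID-19 look-back in the test-negative design applies to cases but not to controls, which lets recent code-only infections into the control group and biases variant VE modestly toward the null

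*Protocol*

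**What the plan says.** Section 10.1 of the protocol defines the two groups of the test-negative design (TND) for Secondary Objectives 16 and 17.

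- **Cases.** The inclusion criterion requires a positive PCR on or after 3/1/2021 with the specimen sent for sequencing, "without a history of a COVID-19 diagnosis code or SARS-CoV-2 positive molecular test in the 90 days prior to the test".
- **Controls.** The same criterion continues after a semicolon: "or tested negative for SARS-CoV-2 by PCR with specimen collected on or after 3/1/2021". No look-back is attached to this branch. On controls, the Matching paragraph adds only that those who "have a negative SARS-CoV-2 molecular test on or after 3/1/2021, and do not have a positive test on or after 3/1/2021 will be defined as" such.
- **Both groups.** One exclusion criterion covers diagnosis codes for cases and controls alike, over a fixed window: "Having a history of a COVID-19 diagnosis code or SARS-CoV-2 positive molecular test between 12/18/2020 and 2/28/2021, inclusive".

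Two other places show how COVID-19 can enter the record as a code without a positive test at KPSC. Section 4.2 describes diagnoses made in 2020 from outside positive tests or from clinical presentation and contact history, "for a total of 56,752 members with a COVID-19 clinical diagnosis only". Section 13 says of outside testing: "Efforts are made to ask patients about positive tests conducted outside of KPSC and to document in the EHR with internal diagnosis codes".

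**The concern.** Controls in a TND should show how common vaccination is among people who could have become cases at the time of their test. Under Section 10.1, a member with a COVID-19 code in the previous 90 days cannot be a case. The same member can be a control if a negative PCR follows and the code is dated 3/1/2021 or later. Controls are therefore drawn partly from people who were not at risk of being counted as cases.

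If the vaccine prevents COVID-19, recent code-only infections are more frequent among the unvaccinated. Admitting them adds unvaccinated people to the control group, lowers its vaccination odds and makes the vaccine look less effective against each variant. At stake are the variant estimates for Objectives 16 and 17. The primary objectives are not affected.

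**Working it through.** **1. What the control rules leave open.**

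| Prior event | Case | Control |
|---|---|---|
| Code or positive test, 12/18/2020 to 2/28/2021 | excluded | excluded |
| Positive test on or after 3/1/2021 | excluded if within the 90 days before the test | excluded |
| Diagnosis code on or after 3/1/2021, within the 90 days before the test | excluded | **eligible** |

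The fixed window does part of the work early on. A 90-day look-back from 3/1/2021 reaches to 12/1/2020, so the window covers most of it. The last test date whose look-back still touches the window is 5/29/2021 (2/28/2021 plus 90 days). After that the window gives controls no protection against recent codes.

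**2. The plan's own sample-size figure.** Section 10.3 states 20 cases for a 1:5 matched TND, with 60% of controls vaccinated, VE 0.8 and 80% power.

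- Vaccinated share in cases: p1 = 0.2 × 0.6 / (0.4 + 0.2 × 0.6) = 0.12 / 0.52 = 0.2308.
- A two-proportion calculation with five controls per case and two-sided alpha 0.025 (Section 10.1) gives 20 cases, with power 0.816 at 20. The figure reproduces.

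**3. How common code-only COVID-19 is (Table 2, year 2020).**

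- Code-only patients: 295,395 − 238,643 = 56,752, as stated in Section 4.2.
- Share of diagnoses: 56,752 / 295,395 = 19.2%.
- Assumed ceiling for contamination: 56,752 / (1,058,157 − 238,643) = 56,752 / 819,514 = 6.9%. This treats every code-only patient as also having had a negative PCR. The true share in the TND is not in the protocol.

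**4. Effect on VE, contamination expressed among unvaccinated controls.** Let c_u be the contaminated share of unvaccinated controls and c_v = OR × c_u that of vaccinated controls. Then OR_obs = OR × (1 − c_v) / (1 − c_u). The 3% value is an assumption, and 7% is the rounded ceiling.

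| True VE | c_u | OR_obs | Estimated VE |
|---|---|---|---|
| 80% | 3% | 0.2 × 0.994 / 0.97 = 0.205 | 79.5% |
| 80% | 7% | 0.2 × 0.986 / 0.93 = 0.212 | 78.8% |
| 40% | 3% | 0.6 × 0.982 / 0.97 = 0.607 | 39.3% |
| 40% | 7% | 0.6 × 0.958 / 0.93 = 0.618 | 38.2% |

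**5. The same, contamination expressed among all controls.** Replace a share f of controls by infected people whose vaccinated share is p1 = 0.2308, so that p_c = 0.6(1 − f) + 0.2308f and OR_obs = 0.3 / [p_c / (1 − p_c)], where 0.3 = p1 / (1 − p1).

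| f | p_c | OR_obs | Estimated VE (true 80%) | Cases needed (alpha 0.025) |
|---|---|---|---|---|
| 0 | 0.6000 | 0.2000 | 80.0% | 20 |
| 1% | 0.5963 | 0.2031 | 79.7% | 20 |
| 5% | 0.5815 | 0.2159 | 78.4% | 22 |
| 6.9% | 0.5744 | 0.2223 | 77.8% | 23 |

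Over f = 1% to 6.9%, a true VE of 50% is estimated as 49.6% to 47.5%, and a true VE of 90% as 89.8% to 88.6%. Step 5 gives larger shifts than step 4 because a given share of all controls is a larger share of the unvaccinated ones.

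**The case against.** **A reader might infer that the protocol contradicts itself by using its own COVID-19 cases as non-cases.** Section 7.2 does say "COVID-19 diagnosis will be defined as a SARS-CoV-2 positive molecular test or a COVID-19 diagnosis code", but it assigns that definition to Primary Objective 1 and Secondary Objectives 1-12 and 14. For Objectives 16 and 17 a case is a PCR-positive specimen sent for sequencing. Classifying TND status by PCR result is coherent, so the documents do not support a charge of contradiction. The defect is the unequal look-back.

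**Direction.** Some codes rest on clinical presentation and contact history. A symptomatic member with such a code and a truly negative PCR is a proper test-negative control, and every false code shrinks the bias. This stands: the direction depends on the codes being true infections.

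**Size.** Nothing in the protocol suggests that every code-only patient also had a negative PCR, so 6.9% is a ceiling. At the planned minimum of 20 cases, an unmatched approximation gives a 97.5% CI of roughly 28% to 94% around a VE of 80%, and a shift of one or two points would not be visible there. It matters more for common variants with tighter intervals. Nor is the 20-case figure undermined: even the ceiling moves it only to 23.

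**Existing protection.** The fixed exclusion window limits the gap for specimens collected up to late May 2021, which is part of the interim period. Table 3 also lists history of COVID-19 diagnosis as a possible covariate. Its inclusion is not assured, however, and as a yes/no item dating from March 2020 it cannot separate a recent episode from a remote one. Neither closes the gap.

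**A wider remedy is tempting:** also dropping controls who receive a code from Day 0 to Day +14. Cases face no such rule, so symmetry does not call for it. It would make control status depend on a label given after the test. If clinicians coded unvaccinated test-negative patients more readily, which is an assumption, the exclusion would itself push VE upward.

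**Conclusion.** The asymmetry is clear in the text, and no other section removes it. Members with a code-only COVID-19 diagnosis dated 3/1/2021 or later and within 90 days of a negative PCR can be controls although they are barred from being cases.

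The consequence is a modest bias toward the null. At a true VE of 80% it is at most about 1 to 2 percentage points at the assumed ceiling of about 7%, and about 0.3 points if 1% of controls are affected. These figures assume that the codes are true infections, that the vaccine protects against code-only disease as well as against the variant studied, and that 2020 counts bound the share in the TND period. The protocol gives no contamination share, so the asymmetry is certain while the size is only bounded by assumption. The point is worth correcting because the correction is cheap. It does not put the variant analysis in doubt.

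**What to change.** In the inclusion criteria of Section 10.1, attach the existing case rule to the test-negative branch: no COVID-19 diagnosis code or positive molecular test in the 90 days before the negative test. Let a member excluded on one negative test contribute another that meets the rule.

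The case rule looks at days before the test, so copying it leaves same-day codes in, as it does for cases. A code exclusion from Day 0 to Day +14 should stay out of the main analysis and serve at most as a sensitivity analysis.

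The cost is one eligibility line, one filter on diagnosis codes already needed for the case rule, and a small loss of candidate controls.

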### Exposures

For the 2-dose analysis, the exposure will be defined as receipt of the second dose of Moderna COVID-19 vaccine  $\geq 14$  days prior to the SARS-CoV-2 test date vs. not receiving a dose of any COVID-19 vaccine prior to the SARS-CoV-2 test date.

For the 1-dose analysis, the exposure will be defined as receipt of only 1 dose of Moderna COVID-19 vaccine  $\geq 14$  days prior to the SARS-CoV-2 test date vs. not receiving a dose of any COVID-19 vaccine prior to the SARS-CoV-2 test date.

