## 10.3 Other considerations

VOCs and VOIs will be selected for analysis based on prevalence in the KPSC population and scientific interest. For a 1:5 matched TND, assuming 60% vaccination rate in test negative

controls, 20 VOC or VOI cases are needed to detect a VE of 0.8 with 80% statistical power. For a 1:1 matched cohort design, approximately 15 VOC or VOI cases are needed in the unvaccinated group to detect a VE of 0.8 with 80% statistical power.

Analyses will be performed at two time points. We will conduct an interim analysis in September 2021 including specimens collected through July 2021 (individuals with VOCs and VOIs and matched test-negative controls). A final analysis will be conducted in April 2022 with specimens collected through February 2022.

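### Test-negative controls must have no positive test up to the data cut, so control selection depends on later infection and variant-specific VE is pushed modestly upward

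*Protocol*

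**What the plan says.** Section 10.1 (Matching) defines controls as members who meet the criteria, have a negative molecular test on or after 3/1/2021, and "do not have a positive test on or after 3/1/2021 will be defined as controls". The same section sets the control's time origin: "The matched date of specimen collection for the negative test will be the index date for the matched control". Controls are matched on age group, sex, race/ethnicity and specimen date within 10 days.

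Cases carry no condition on later tests: "For individuals who have more than one positive test after 3/1/2021, sequencing data from the first specimen will be included in analyses". The infection-history rules in Section 10.1 look back only. A positive test qualifies if it is "without a history of a COVID-19 diagnosis code or SARS-CoV-2 positive molecular test in the 90 days prior to the test", and a fixed exclusion covers 12/18/2020 to 2/28/2021. Exposure is fixed at the test date: for the 2-dose analysis it is "receipt of the second dose of Moderna COVID-19 vaccine" at least 14 days earlier, against no dose of any COVID-19 vaccine.

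Section 10.3 sets two data cuts. The interim analysis uses specimens through July 2021. For the other, "A final analysis will be conducted in April 2022 with specimens collected through February 2022".

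**The concern.** Every other element of the test-negative design is settled by the specimen date; control status is not. A member who tests negative in April 2021 and first tests positive in January 2022 cannot serve as a control for an April 2021 case, because of an event nine months after the match. Matching on specimen date does not help: it fixes when the negative test was taken, not how far ahead eligibility is judged.

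If the vaccine protects, members unvaccinated at the matched date are more likely to record a later positive test and so to be dropped. The retained controls then contain too many vaccinated members, and the odds ratio is too low. This is the familiar difference between drawing controls from those still uninfected at the end and drawing them from those at risk at the case's date. More data do not remove it.

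The look-ahead shortens as the index date approaches the cut. The distortion therefore tends to be greater for variants seen early than for those seen late, and the same early cases can give different VE at the two cuts. Section 10.1 also plans VE by time since vaccination. If longer times since vaccination fall at later index dates, they carry less inflation, which could resemble waning. That last effect is not quantified here.

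**Working it through.** **The plan's own figure.** The protocol gives no figure for this bias. Its only sample-size figure for the test-negative design is 20 cases (Section 10.3: 1:5 matching, 60% of controls vaccinated, VE 0.8, 80% power). With an odds ratio of 0.2, the vaccinated share among cases is 0.6 × 0.2 / (0.4 + 0.6 × 0.2) = 0.231. The two-proportion formula with 5 controls per case at two-sided alpha 0.025 gives 19.3, so 20. The figure reproduces and does not depend on the control rule.

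**Formula.** Let r_u and r_v be the probabilities that a control unvaccinated or vaccinated at the index date has a recorded positive test between that date and the cut. Retained controls have their odds of vaccination multiplied by (1 − r_v)/(1 − r_u), so

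OR observed = OR true × (1 − r_u)/(1 − r_v).

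If the same VE applies to later infection and vaccination status does not change, r_v = 1 − (1 − r_u)^(1 − VE), and the factor reduces to (1 − r_u)^VE.

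**Input for r_u.** Section 9 plans for 30 diagnoses per 1,000 unvaccinated members over 4 months, that is 7.5 per 1,000 per month, or about 9% over 12 months.

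**Worst case (12-month look-ahead, r_u = 0.09).**
- True VE 80%: factor 0.91^0.8 = 0.927; OR 0.2 × 0.927 = 0.1855; VE reads 81.5%.
- True VE 50%: factor 0.91^0.5 = 0.954; OR 0.5 × 0.954 = 0.477; VE reads 52.3%.
- Treating 0.0075 per month as a hazard instead gives r_u = 1 − exp(−0.09) = 8.6%, and readings of 81.4% and 52.2%.

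**By index date and cut.** With m months of look-ahead from mid-month, the factor is exp(−0.0075 × m × VE).

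| Index month, cut | m | True 80% reads | True 50% reads |
|---|---|---|---|
| March 2021, February 2022 | 11.5 | 81.3% | 52.1% |
| September 2021, February 2022 | 5.5 | 80.7% | 51.0% |
| February 2022, February 2022 | 0.5 | 80.1% | 50.1% |
| March 2021, July 2021 | 4.5 | 80.5% | 50.8% |

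For the same March 2021 cases, the reading moves between cuts by 0.8 points at true VE 80% and 1.3 points at 50%.

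**Later vaccination of controls.** Assume 10% of the still unvaccinated are vaccinated each month, with monthly risk 0.0075 while unvaccinated and 0.0075 × (1 − VE) afterwards, over 12 months. Stepping month by month:
- VE 80%: 1 − r_u = 0.9409, 1 − r_v = 0.9821, factor 0.958; reads 80.8%.
- VE 50%: 1 − r_u = 0.9305, 1 − r_v = 0.9559, factor 0.973; reads 51.3%.

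The sign stays; the size falls by roughly 40%.

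**Higher later positivity (an assumption, not a document figure).** At r_u = 25% with VE 80% against later infection, r_v = 0.25 × 0.2 = 5% and the factor is 0.75/0.95 = 0.789. True VE 80% reads 84.2%. A variant with true VE 50% reads 60.5%.

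**The case against.** The strongest objection is about size and weight. At the planning incidence the shift is at most about 1.5 points near VE 80%. With 20 cases and 100 controls, an unmatched approximation gives SE(log OR) = √(1/4.6 + 1/15.4 + 1/60 + 1/40) = 0.57, and a 97.5% interval for VE 80% of about 28% to 94%. One point is negligible beside that, though less so for a common variant. Objectives 16 and 17 are secondary, and Section 3 says secondary objectives may be underpowered. This stands.

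A reader might take later positivity from Section 4.2: "There were 238,643 members testing positive", out of 1,058,157 members tested, is 22.6%, which would turn a true 80% into 83.7%. The documents do not support that use. The figure is 2020 positivity among everyone tested, when testing first favoured people with symptoms; it is not the risk of a positive test after a negative one. Dividing by all members aged 12 or over in Table 1 (341,464 + 2,942,731 + 432,045 + 270,091 = 3,986,331) gives 6.0%, at which 80% reads 81.0% and 50% reads 51.5%. That denominator is only approximate, and members who seek testing may be at higher risk than the membership average, so neither ratio settles r_u.

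Two further points stand. Section 4.1 shows eligibility opening to everyone aged 16 and over in April 2021 and 12 and over in May, so many early unvaccinated controls could be vaccinated soon after, which weakens the gradient where the look-ahead is longest. And healthcare workers were prioritised for vaccination, while Section 4.2 describes voluntary weekly testing of patient-facing staff; more detection among vaccinated members would work against the upward shift.

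The rule does keep cases and controls disjoint and removes some false-negative controls. Screening false negatives needs only a short window, and overlap is acceptable in date-matched sampling, so neither justifies a look-ahead of up to a year.

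**Conclusion.** The control definition as written conditions on events after the index date, and nothing in Sections 10.1 to 10.3 or in the Limitations corrects or acknowledges this. The upward direction follows if vaccination lowers the chance of a later recorded positive test; it is not guaranteed if vaccinated members are tested more often.

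At the protocol's planning incidence, with constant VE and no later vaccination, the worst-case shift is from 80% to about 81.5% and from 50% to about 52.3%. It falls to 80.8% and 51.3% if 10% of unvaccinated controls are vaccinated per month. Shifts of 4 to 10 points need later positivity near 25%, which the documents do not supply.

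A reader might infer that the variant results would be invalid or that the primary objectives are affected. Neither follows: the planned size of the effect is small, and the primary objectives use a separate cohort analysis. This is a recommended correction to a secondary-objective analysis, not a must-fix.

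**What to change.** In Section 10.1, define a control as a member with a negative test and no positive test from 3/1/2021 up to the control's index date. A short fixed window after that date may be added to screen out false negatives. State that a control may become a case later. Apply the rule at both the interim and the final analysis, and report the present definition as a sensitivity analysis.

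With no look-ahead the factor is 1 and this source of bias disappears; a short window leaves only a trace of it. The cost is one sentence, a re-run of control selection from data already held, and some members appearing both as a control and as a later case. The 20-case figure is unchanged.
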